# Tamoxifen in Duchenne muscular dystrophy (TAMDMD): study protocol for a multicenter, randomized, placebo-controlled, double-blind phase 3 trial

**DOI:** 10.1186/s13063-019-3740-6

**Published:** 2019-11-21

**Keywords:** Duchenne muscular dystrophy, Tamoxifen, Motor function measure, 6-min walk test, Quantitative muscle MRI, Randomized placebo-controlled trial

## Abstract

**Background:**

Duchenne muscular dystrophy (DMD) is an inherited neuromuscular disorder of childhood with a devastating disease course. Several targeted gene therapies and molecular approaches have been or are currently being tested in clinical trials; however, a causative therapy is still not available and best supportive care is limited to oral glucocorticoids with numerous long-term side effects. Tamoxifen is a selective estrogen receptor regulator, and shows antioxidant actions and regulatory roles in the calcium homeostasis besides its antitumor activity. In a mouse model of DMD, oral tamoxifen significantly improved muscle strength and reduced muscle fatigue. This multicenter, randomized, double-blind, placebo-controlled phase III trial aims to demonstrate safety and efficacy of tamoxifen over placebo in pediatric patients with DMD. After completion of the double-blind phase, an open-label extension of the study will be offered to all participants.

**Methods/design:**

At least 71 ambulant and up to 20 nonambulant patients with DMD are planned to be enrolled at multiple European sites. Patients will be randomly assigned to receive either tamoxifen 20 mg or placebo daily over 48 weeks. In the open-label extension phase, all patients will be offered tamoxifen for a further 48 weeks. The primary endpoint of the double-blind phase is defined as the change of the D1 domain of the motor function measure in ambulant patients or a change of the D2 domain in nonambulant patients under tamoxifen compared to placebo. Secondary outcome measures include change in timed function tests, quantitative muscle testing, and quantitative magnetic resonance imaging of thigh muscles. Laboratory analyses including biomarkers of tamoxifen metabolism and muscle dystrophy will also be assessed.

**Discussion:**

The aim of the study is to investigate whether tamoxifen can reduce disease progression in ambulant and nonambulant patients with DMD over 48 weeks. Motor function measures comprise the primary endpoint, whereas further clinical and radiological assessments and laboratory biomarkers are performed to provide more data on safety and efficacy. An adjacent open-label extension phase is planned to test if earlier initiation of the treatment with tamoxifen (verum arm of double-blind phase) compared to a delayed start can reduce disease progression more efficiently.

**Trial registration:**

ClinicalTrials.gov, NCT03354039. Registered on 27 November 2017.

## Background

Duchenne muscular dystrophy (DMD) is the most common neuromuscular disorder in childhood with an X-linked inheritance and an incidence of up to 1 in 5000 males [1, 2]. The severe and progressive weakness of skeletal muscles leads to loss of ambulation in 22% to 56% of the cases, whereas the concomitant impairment of cardiac and respiratory muscles accounts for an early mortality [2].

The clinical and pathological phenotype of DMD is caused by mutations in the dystrophin gene, which results in the total loss of dystrophin protein expression in the muscle cells [3]. Dystrophin has a major role in sarcolemmal stabilization by linking the internal actin cytoskeleton to the extracellular matrix. The protein is part of the dystrophin-associated protein complex (DAPC) including numerous integral and peripheral membrane proteins [4]. The lack of dystrophin leads to destabilization of the DAPC and to increased vulnerability and leakage of the cell membrane [5]. There is also growing evidence that the DAPC has a role in intracellular signaling pathways due to its association with several kinases, phosphatases, ion channels, receptors and transporters, pathways which seem to have significance in the disease pathogenesis [5]. If dystrophin is missing, its downstream processing is dysregulated, leading to increased Ca^2+^ influx, oxidative stress and mitochondrial dysfunction [6]. An increased cytosolic Ca^2+^ level is a result of many dysfunctional pathways involving store-operated channels, stretch-activated channels, the sarcolemmal Ca^2+^ pump and calpains [5, 7, 8]. Increased intracellular Ca^2+^ levels were shown in mdx mice and also in muscle biopsies from DMD patients [9–12], implicating Ca^2+^ as a main driver of the pathology responsible for apoptosis and necrosis. It has even been shown that increased Ca^2+^ influx alone is sufficient to induce muscular dystrophy through transient receptor potential canonical 3-mediated pathways [13].

Several targeted gene therapies and molecular approaches counteracting the dysfunctional intracellular pathways have been tested in *mdx* animal models and many are currently investigated in clinical trials [6, 14]. However, the proof of principle for DMD patients has yet to be established. Tamoxifen is a selective estrogen receptor regulator and its use is well established in patients with breast cancer [15]. Tamoxifen acts as an agonist or antagonist of estrogen in a tissue-dependent manner. Advantages of tamoxifen include its antioxidant actions and regulatory roles in calcium homeostasis [16–18]. Based on preliminary data provided by the investigator, tamoxifen leads to an elevated level of pro-inflammatory cytokines and growth factors involved in muscle regeneration and fibrosis (transforming growth factor-β (TGFβ), insulin-like growth factor 1 (IGF1) and osteopontin) and to an increased capacity of muscle-purified mitochondria to buffer cytosolic calcium. Tamoxifen is able to prevent bone loss and has been shown to increase the height of short boys by decreasing the rate of bone maturation [19, 20]. In a mouse model of DMD, oral tamoxifen stabilized the membrane of myofibers, significantly improved muscle strength, reduced muscle fatigue, and slowed phenotype [21, 22]. Furthermore, tamoxifen could reduce fibrosis of the heart muscle and diaphragm by about 50%. The effectiveness of tamoxifen has recently been shown in another fatal congenital muscular disorder. In a mouse model of myotubular myopathy, tamoxifen could improve force, decrease disease progression and prolong survival [23, 24].

Preclinical and clinical data for tamoxifen in muscular dystrophy are promising and the findings suggest its usage also in patients with DMD. According to yet unpublished preliminary results of an open-label trial (ClinicalTrials.gov identifier NCT02835079), tamoxifen has beneficial effects at a daily dose of 20 mg. Based on personal communication with the investigator, patients with DMD taking tamoxifen remained stable over an observation time of 12 month as assessed by North Star Ambulatory Assessment (NSAA) and timed function tests (TFT) including the 6-min walk test (6MWT). Furthermore, all patients showed good tolerance of the medication without any treatment-related serious adverse events. Tamoxifen has also been previously tested in the pediatric population for low- and high-grade glioma, desmoid tumor, pubertal gynecomastia and short height [25–28]. Treatment with tamoxifen was well tolerated in each study, even when used at higher doses.

The purpose of this study is to evaluate the effect of tamoxifen on muscle function and muscle force compared to placebo in ambulant and nonambulant children with DMD. Furthermore, regular pharmacokinetic evaluation of tamoxifen plasma levels and metabolites, and detailed analysis of biomarkers of muscle degeneration, muscle necrosis (e.g., creatine kinase (CK) and alkaline phosphatase (AP)) and muscle dystrophy (e.g., tumor necrosis factor (TNF), TGFβ, interleukin (IL)-1β and IL-6) could provide a better understanding of the mode of action of tamoxifen. With the current lack of an effective and safe long-term treatment for DMD patients, tamoxifen could be a milestone in improving clinical outcome while providing good safety and tolerability.

## Methods/design

### Study design

This is an investigator-initiated, multicenter, randomized, double-blind, placebo-controlled phase III efficacy and safety trial in patients with DMD. This part of the study is conducted over 48 weeks. The two treatment arms include tamoxifen (verum) and placebo (control). We plan to enroll at least 71 ambulant patients aged between 6.5 and 12 years (group A) and 16–20 nonambulant patients aged between 10 and 16 years (group B) at multiple European sites (Belgium, France, Germany, Netherlands, Spain, Switzerland, Turkey, and the United Kingdom). After completion of the double-blind phase, all participants will be offered the option of taking part in an open-label extension (OLE) trial of the main study. In this part, all patients will receive tamoxifen for 48 weeks.

The trial was approved by the local ethics committee (ethics committee of both Basel cantons, 2017–01708), the National Swiss Drug Agency (Swissmedic, 2018DR3068), the European Union Drug Regulating Authorities Clinical Trials (EudraCT 2017–004554-42), and the European Union Drug Regulating Authorities Pharmacovigilance (EudraVigilance). The study was registered at ClinicalTrials.gov (NCT03354039) and at the Swiss National Clinical Trials Portal (SNCTP000002387) prior to recruitment. The SPIRIT flow chart showing the main study design is seen in Fig. 1, while Fig. 2 represents the study design of the OLE phase. The Recommendations for Interventional Trials (SPIRIT) checklist on which the study protocol is based is presented as Additional file 1.

**Fig. 1 Fig1:**
[figure not shown]
Flow chart showing the study design of the placebo-controlled, double-blind phase of the tamoxifen in Duchenne muscular dystrophy (TAMDMD) study. *For those patients who do not enter the open-label extension phase. RCT randomized controlled trial, V visit

**Fig. 2 Fig2:**
[figure not shown]
Flow chart showing the study design of the open-label extension phase (OLE) of the tamoxifen in Duchenne muscular dystrophy (TAMDMD) study. IMP investigational medicinal product, TAM tamoxifen

### Inclusion criteria

Only male patients with a molecular diagnosis of DMD are included in the study. Ambulant patients in group A must fulfill the following criteria at screening: 6.5 to 12 years of age, weight >20 kg, stable treatment with glucocorticoids >6 months, ability to walk at least 350 m without assistance in 6MWT and a D1 domain of the motor function measure (MFM) >40%. Nonambulant patients in group B must be between 10 and 16 years of age at time of screening, be off glucocorticoids for >6 months, and have no ability to walk more than 10 m. Patients taking ataluren should be under a stable ataluren treatment for at least 3 months or be off ataluren treatment for at least 3 months before screening. For participation in the OLE trial, a preceding completion of the main study is mandatory.

### Exclusion criteria

Patients fulfilling the following criteria are excluded from the study: females, allergy to tamoxifen, use of tamoxifen or testosterone within the last 3 months, known or suspected malignancy, clinically relevant disease with limitation of renal, liver or heart function, injury impacting functional testing, planned or expected spinal fusion surgery during the study period, previous spinal fusion surgery within the last 6 months, galactosemia, congenital lack of lactase, and glucose-galactose malabsorption. Patients taking CYP2D6 inhibitors, CYP3A4 inducers, platelet aggregation inhibitors, coumarin-type anticoagulants, or drugs metabolized by CYP2C9 must also be excluded. Furthermore, patients with certain eye disorders (cataract, retinopathy, optic neuropathy, alteration of the cornea) and those with laboratory abnormalities such as anemia, thrombocytopenia, leukopenia, neutropenia or agranulocytosis are also not allowed to be included. Patients taking part in the trial should not concomitantly participate in any other interventional trial or have done up to 3 months prior to screening.

### Randomization and blinding

Patients who meet the study admission criteria and do not fulfill any exclusion criteria are enrolled and randomly assigned to either the active treatment or the control treatment with a treatment allocation of 1:1. The study is double-blind; therefore, all clinical investigators and all patients and their caregivers will remain blinded throughout the trial. Patients who withdraw from the study will not be replaced. At the end of the main trial all patients will be asked to join the OLE trial, receiving active treatment only. Participants can leave the study at any time and for any reason.

### Intervention

All patients who undergo randomization will receive an oral drug once daily: either tamoxifen at a dose of 20 mg (verum) or placebo (control). The placebo medication will have the same texture, taste and color as the interventional drug, but without any active ingredients. Both the interventional and the control drug are manufactured by Hexal AG, [name]. Tamoxifen tablets will be protected from light and moisture.

The intervention period lasts 48 weeks with an end-of-study visit at week 60. The study medication is taken on top of standard care with glucocorticoids in group A if treatment with steroids has been stable over the last 6 months prior to screening (dose adaptations according to weight change are allowed). After completing the main study, an OLE is performed where all patients will be offered to receive tamoxifen.

### Study procedure

Patients enrolled in the study attend a screening visit 4 weeks prior to baseline. Study visits take place every 12 weeks during the intervention period of 48 weeks. The double-blind phase of the study ends with a visit at week 48, with a follow-up visit at week 60 for patients not participating in the extension phase.

At screening (visit 0), patients and their caregivers receive detailed information about preclinical data, the study procedure and possible benefits and risks of the trial. After signing the informed consent form, inclusion and exclusion criteria will be verified. Patients/caregivers are asked to sign a separate optional informed consent form for collection of data for further genetic and biomarker analysis. Patients fulfilling the criteria will be enrolled and undergo the following investigations: physical examination, vital signs, blood draw for safety laboratory tests, and physiotherapy assessment including MFM, NSAA, proximal upper limb function (PUL), TFT (6MWT, 10-meter walk/run test (10MWT), time to rise from the floor), and quantitative muscle testing (QMT) using grip force. An ophthalmological examination including visual acuity and slit lamp is performed either at screening or in the time period between screening and baseline.

The baseline visit (visit 1) takes place no longer than 4 weeks after screening. During this visit, fulfillment of the inclusion/exclusion criteria are reassessed and qualified patients randomized to receive the study medication (verum or placebo). During this visit, the following procedures are performed: physical examination, vital signs, Tanner staging (assessment of the external primary and secondary sex characteristics), blood draw, adverse events, calculation of Wells score (risk estimation for deep vein thrombosis), complete physiotherapy assessment as described above, quantitative magnetic resonance imaging (qMRI) of the thigh muscle measuring the mean fat fraction (FF) and T2 relaxation time (T2), ophthalmological examination, patient-reported outcome measures using the Personal-Adjustment and Role Skills Scale (PARS-III) and Raven’s Coloured Progressive Matrices (RCPM). In selected sites, an x-ray for bone age determination and dual-energy x-ray absorptiometry (DEXA) will be performed during this visit.

Six weeks after baseline, patients receive a telephone call to capture any early adverse events and to assess the Wells score.

At weeks 12 and 36 (visits 2 and 4, respectively) the following procedures will be performed: physical examination, vital signs, adverse events, blood draw, Wells score, and complete physiotherapy assessment.

At weeks 24 and 48 (visits 3 and 5, respectively) the following procedures will be performed: physical examination, vital signs, Tanner staging, blood draw, Wells score, complete physiotherapy assessment, qMRI, ophthalmological examination, and PARS-III. At week 48, RCPM will be repeated and, in selected sites, x-ray bone age determination and DEXA will be performed. For patients not participating in the OLE phase, a follow-up visit takes place at week 60 (visit 6) and includes the following: physical examination, vital signs, adverse events, blood draw, and Wells score.

Informed consent for the OLE phase will be offered to all patients/caregivers already at screening, but withdrawal from the extension phase is possible at any time throughout the study. Patients confirming their participation in the OLE phase will be re-checked for the inclusion and exclusion criteria at week 48 (1OLE). All patients will receive a telephone call 6 weeks after starting the OLE and are asked for early adverse events and to evaluate the Wells score. Study visits will be performed every 12 weeks and include the same assessments as the main study. At weeks 60 (2OLE) and 84 (4OLE) the following procedures will be performed: physical examination, vital signs, adverse events, blood draw, Wells score, and complete physiotherapy assessment. At weeks 72 (3OLE) and 96 (5OLE) the following procedures will be performed: physical examination, vital signs, Tanner staging, blood draw, Wells score, complete physiotherapy assessment, qMRI, ophthalmological examination, and PARS-III. During 5OLE, RCPM will be repeated and, in selected sites, x-ray bone age determination and DEXA will be performed. For all patients in the OLE, a follow-up visit at week 102 (6OLE) is planned including physical examination, vital signs, adverse events, blood draw and Wells score. Tables 1 and 2 show the detailed schedule of the placebo-controlled, double-blind randomized controlled trial and the OLE phase of the study, respectively.

**Table 1 Tab1:**
[figure not shown]
Detailed schedule of the placebo-controlled, double-blind phase of the tamoxifen in Duchenne muscular dystrophy (TAMDMD) study

^1^General pediatric physical examination, including anthropometric measurements (weight and height). ^2^Blood pressure and heart rate. ^3^Including visual acuity and slit-lamp examination. ^4^Motor function measurement, North Star Ambulatory Assessment, proximal upper limb function, timed function tests including 6-min walk test, 10-min walk/run test, supine up time, and quantitative muscle testing using grip force. ^5^Thigh muscle fat fraction and T2 relaxation time on quantitative magnetic resonance imaging (MRI). ^6^Personal-Adjustment and Role Skills Scale. ^7A^Chemistry: creatine kinase, gamma GT, total bilirubin, alkaline phosphatase, creatinine, electrolytes (Na^+^, K^+^, Ca^2+^), urea, triglycerides; hematology: full blood count for erythrocytes, leukocytes (with a differential), platelets, hemoglobin, hematocrit, absolute neutrophil count. ^7B^Sex hormone function (luteinizing hormone, follicle-stimulating hormone, testosterone, sex hormone binding globulin, alpha-fetoprotein), preservation of serum and EDTA full blood to be able to measure plasma levels of tamoxifen and its metabolites (endoxifen and 4-OH-tamoxifen) and biomarkers I (connective tissue growth factor, fibroblast growth factor 21, insulin growth factor 1, interleukin (IL)-1β, IL-6, matrix metalloproteinase (MMP)-2, MMP-9, osteopontin, platelet-derived growth factor (PDGF)-A, PDGF-B, tissue inhibitor of metalloproteinases 1, transforming growth factor-β, tumor necrosis factor. ^8^Biomarkers II: Cyp2D6, Cyp3A4. ^9^In selected sites only. ^10^Only for patients not participating in the open-label extension phase. d day, DEXA dual-energy x-ray absorptiometry, DVT deep vein thrombosis, TC telephone call

**Table 2 Tab2:**
[figure not shown]
Detailed schedule of the open-label extension phase (OLE) of the tamoxifen in Duchenne muscular dystrophy (TAMDMD) study

^1^General pediatric physical examination, including anthropometric measurements (weight and height). ^2^Blood pressure and heart rate. ^3^Including visual acuity and slit-lamp examination. ^4^Motor function measurement, North Star Ambulatory Assessment, proximal upper limb function, timed function tests including 6-min walk test, 10-min walk/run test, supine up time, and quantitative muscle testing using grip force. ^5^Thigh muscle fat fraction and T2 relaxation time on quantitative magnetic resonance imaging (MRI). ^6^Personal-Adjustment and Role Skills Scale. ^7A^Chemistry: creatine kinase, gamma GT, total bilirubin, alkaline phosphatase, creatinine, electrolytes (Na^+^, K^+^, Ca^2+^), urea, triglycerides; hematology: full blood count for erythrocytes, leukocytes (with a differential), platelets, hemoglobin, hematocrit, absolute neutrophil count. ^7B^Sex hormone function (luteinizing hormone, follicle-stimulating hormone, testosterone, sex hormone binding globulin, alpha-fetoprotein). ^8^In selected sites only. *Will be assessed at visit 5 (end of study visit). d day, DEXA dual-energy x-ray absorptiometry, DVT deep vein thrombosis, TC telephone call

### Quality assurance

This study will be conducted in compliance with the protocol, the current version of the Declaration of Helsinki, the Good Clinical Practice from the International Council for Harmonization (ICH-GCP) and with all national legal and regulatory requirements. To achieve this the members of the study team are required to hold an updated certification in GCP. All physiotherapists will be trained and certified for motor function measurements. To control adherence to the intervention, a qualified person from the study team will check the number of dispensed/taken medications and complete a study-specific drug accountability form at each visit. A distributor (Thermo Fisher Scientific, Allschwil, Switzerland), who is not involved in the study, will pack, label and dispense the medication according to the randomization procedure to prevent unblinding of the investigators.

### Safety assessments

Adverse events will be monitored throughout the study. At every visit patients and their caregivers will be asked about adverse events. Measurement of vital parameters (blood pressure, heart rate, electrocardiogram), physical examination, and assessment of the Wells score will be performed. Safety laboratory measurements include full blood count, CK, AP, gamma-glutamyl transferase (gamma GT), total bilirubin, urea, creatinine, electrolytes, and triglyceride levels. Further laboratory assessments (such as luteinizing hormone (LH), follicle-stimulating hormone (FSH), testosterone, sex hormone binding globulin (SHBG), alpha-fetoprotein (AFP), plasma levels of tamoxifen and its metabolites, and biomarkers) will be performed at defined time points during the study (Figs. 1 and 2). Visual acuity and split-lamp examinations performed by an ophthalmologist or optician and Tanner staging are performed at three study visits both during the intervention and the OLE phase. RCPM will be performed at two time points in both the intervention and the OLE phases. X-ray bone age determination and DEXA scan are planned only in selected sites. A safety follow-up will take place for patients with early study termination and include the following: assessment of adverse events, vital parameters, physical examination, safety blood test and biomarkers, Tanner staging, Wells score, ophthalmological examination, RCPM, physiotherapeutic evaluation and DEXA scan at selected sites.

The study medication must be immediately discontinued in the following cases: decrease in visual acuity of more than 30% compared to baseline, cataract or optic nerve involvement or any other significant novel eye disease, thromboembolic event, newly diagnosed malignancy, or any other severe drug-related adverse events or serious adverse events. Also, laboratory abnormalities including platelet count <75 × 10^9^/l, absolute neutrophil count <1 × 10^9^/l and serum Ca^2+^ >2.6 mmol/l must lead to treatment discontinuation. Furthermore, withdrawal of consent, patient noncompliance, logistical reasons, or inability to attend study visits can also lead to early patient termination from the study. Finally, in case of negative (nonsignificant) differences of the primary endpoint after analysis of the randomized controlled trial phase, the OLE phase will be finished and the active treatment stopped immediately in all study patients.

All serious adverse events must be reported to the Sponsor-Investigator of the study within 24 h after an investigator becomes aware of such an event. In the case of life-threatening serious adverse events or those resulting in death, the local national Ethics Committee must also be informed within 7 days. Patients with adverse events will be followed up by the investigator for up to 30 days after the last visit.

Both patients and their partners of child-bearing potential must employ a reliable method of birth control during the study and for a further 90 days after the intake of the study drug. Special attention must be paid to protection from the sun throughout the trial and up to at least 12 weeks after the trial ends. In case of problems and safety concerns that cannot be solved with on-going blinded treatment, the participant’s allocated intervention will be revealed. Unblinding can be performed by the investigators using the randomizer.at tool. Any important protocol modifications will be directly communicated to all relevant parties. Under emergency circumstances, deviations from the protocol to protect the rights, safety and well-being of human subjects may proceed without prior approval of the sponsor and the ethics committee. Deviations must be documented and reported to the sponsor and the ethics committee as soon as possible.

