### Statistical analysis

#### Primary analysis

The primary analysis will be based on the D1 domain of the MFM in ambulant patients. For both groups A and B, two analysis sets will be built. The full analysis set will include all patients who had at least one follow-up measurement at week 24 or later. The per-protocol set will include all patients from the full analysis set who had the 1-year follow-up visit, and who had a drug compliance of 70–100%. The analysis will be done on the intention-to-treat principle. The measurement at randomization (week 0) will be considered as the baseline and the measurement at week 48 as the primary endpoint. An ANCOVA approach will be used: D1 at 48 weeks will be modeled using a linear regression model including D1 at baseline and treatment groups (verum versus placebo) as predictors in the model. Medication with glucocorticoids will be included as a covariable. Since D1 can be performed only in ambulant patients, this patient group will be used for the primary analysis. The model will be controlled by checking the model assumptions and by inspecting the residuals and leverages.

A following sensitivity analysis will be done to support the main analysis: concomitant use of CYP2D6 inhibitors in the treatment arm as an interaction term, glucocorticoid use in the treatment arm as an interaction term, exclusion of adjustment for glucocorticoid use, exclusion of multiple imputations (the last observation available at least 24 weeks after randomization will be imputed for missing values), inclusion of all measurements at weeks 0, 12, 24, 36, and 48 in a mixed -effects model, and repetition of the analysis on the per-protocol dataset.

For further efficacy analysis, the previously described ANCOVA approach (based on the primary outcome measure) will be performed also for the OLE phase.

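### Noncompliance is allowed to end study participation, and stopping drug is not clearly separated from leaving the study, so the week-48 D1 needed for intention to treat may go unmeasured

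*Protocol article*

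**What the plan says.** The Safety assessments section uses two kinds of wording. For eye findings, thromboembolic events, malignancy and severe or serious adverse events it says "The study medication must be immediately discontinued in the following cases". For three laboratory limits it says that these "must lead to treatment discontinuation". Both concern the medication. It then adds that "withdrawal of consent, patient noncompliance, logistical reasons, or inability to attend study visits can also lead to early patient termination from the study". That sentence concerns the study.

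The same section provides for boys who leave early: "A safety follow-up will take place for patients with early study termination". The list of procedures for that contact ends with "RCPM, physiotherapeutic evaluation and DEXA scan at selected sites". The Study procedure section describes physiotherapy assessments that include the MFM, so D1 is probably recorded at exit. Nothing in the article says that a boy who has stopped drug, or takes it irregularly, continues to week 48.

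The Primary analysis section states: "The analysis will be done on the intention-to-treat principle", and "The measurement at randomization (week 0) will be considered as the baseline and the measurement at week 48 as the primary endpoint". The full analysis set requires a follow-up measurement at week 24 or later. On the other set it says: "The per-protocol set will include all patients from the full analysis set who had the 1-year follow-up visit", and it adds a compliance condition of 70–100%. Multiple imputation is implied for the main analysis, because leaving it out is listed as a sensitivity analysis. In that sensitivity analysis the last value from week 24 onward stands in for a missing one.

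**The concern.** An intention-to-treat comparison at week 48 needs the week-48 outcome of every randomised boy, whatever he did with his tablets. Noncompliance arises after randomisation and may depend on treatment. It does not prevent a boy from attending an MFM assessment. Removing him for that reason creates a missing value that could be avoided.

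The words that join the study-exit sentence to the drug-stopping rules (furthermore, also) leave room for a site to treat a safety stop as the end of participation. The last D1 of such a boy would then mostly reflect time on drug. Imputing or carrying that value forward moves the result towards an on-treatment effect, while the report calls it intention to treat. A boy who leaves before week 24, with no later measurement, drops out of the full analysis set altogether.

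**Working it through.** **The passages side by side.** The per-protocol set has two conditions, the 1-year visit and 70–100% compliance. The second adds something only if some boys attend the 1-year visit with compliance outside that range. The analysis section therefore expects noncompliant boys to remain and be measured, while the safety section permits their removal. Because the removal is permissive, both texts can be followed: some leave and some stay. Who stays is then decided case by case, on a variable that treatment may influence.

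**The plan's own figures** (Sample size estimation): 60 evaluable, 15% drop-out, 10% screening failure, losses of 9 points on placebo and 4.5 on tamoxifen.
- Randomised: 60 / 0.85 = 70.6, so 71. Screened: 71 / 0.90 = 78.9, so 79. Both reproduce.
- Accepted as not evaluable: 71 − 60 = 11, and 11 / 71 = 15.5%. The article does not say how many of these would be drug stoppers or noncompliant.
- The 60 itself came from resampling pilot data that are not shown, so it cannot be reproduced.

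**Illustration 1: imputed like completers.** Assume that a share p of the tamoxifen arm stops, keeps a fraction k of the 4.5-point effect, and is imputed as if still benefiting fully. Placebo stoppers imputed like placebo completers add no error. Overstatement = 4.5 × p × (1 − k).

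| p | k = 0 | k = 0.5 |
|---|---|---|
| 5% | 0.23 | 0.11 |
| 10% | 0.45 | 0.23 |
| 15.5% | 0.70 | 0.35 |
| 20% | 0.90 | 0.45 |

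**Illustration 2: week-24 value carried forward** (sensitivity analysis only). Assume linear decline, all stops at week 24, and the placebo slope afterwards. A placebo stopper is recorded as losing 9 × 24/48 = 4.5 instead of 9. A tamoxifen stopper is recorded as losing 2.25 instead of 2.25 + 4.5 = 6.75. Each error is 4.5 points, and they act in opposite directions on the difference. The net error is 4.5 × (tamoxifen share − placebo share).
- 6/35 and 5/36 stoppers: 4.5 × (0.171 − 0.139) = 0.15 on a true 4.11 (4%).
- 8/35 and 3/36: 4.5 × (0.229 − 0.083) = 0.65 on a true 3.99 (16%).
- Equal shares: zero. If more boys stop on placebo, the sign reverses.

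**Does the fix need more patients?** No SD is given. Assuming two-sided 0.05 and a simple two-sample comparison, 80% power with 30 per arm implies SD = 4.5 / [(1.960 + 0.842) × √(2/30)] = 6.2. Suppose all 11 are followed to week 48, spread evenly over the arms. The difference is 4.5 × [1 − (11/71)(1 − k)], which gives:
- k = 1: 4.50 points, power 86% at N = 71;
- k = 0.5: 4.15 points, power 80%;
- k = 0: 3.80 points, power 73%.

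The planned 80% is kept if these boys retain about half of the effect.

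**The case against.** Several stronger readings are tempting, and the article does not support them.
- A reader might infer that every boy who stops drug is out of the study. The safety and laboratory rules stop medication only; exit from the study is an inference from the linking words.
- A reader might infer that noncompliant boys must be removed. The sentence says only that noncompliance can have this result.
- A reader might conclude that D1 is never measured in those who leave. A physiotherapy evaluation is planned at early termination, though generally not at week 48.
- A reader might say that the two sections cannot both be followed. They can, as shown above.

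The size is also open to challenge. Withdrawn consent and inability to attend are largely unavoidable losses, and the article gives no reasons for its 15%. Nothing in it supplies an imbalance between arms. The open-label experience mentioned in the Background section reports good tolerance without treatment-related serious events. An extreme 10/1 split would give a 30% overstatement under carry-forward, but that split has no source and carry-forward is not the main analysis. The imputation model is not shown, so imputation like completers is an assumption. With the implied SD of 6.2, the standard error of the difference is 6.2 × √(2/30) = 1.6 at 60 boys, larger than any entry in the table.

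Finally, this is an article condensed from protocol version 8.0, and rules for visits after stopping drug may stand there. That answers the silence on follow-up of drug stoppers. It does not answer the sentence on noncompliance, which is a stated rule that a fuller text would have to contradict, not merely extend.

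**Conclusion.** The point holds in a limited form. The article permits removal from the study for noncompliance and leaves the line between stopping drug and leaving the study unclear. Both fit poorly with an intention-to-treat analysis of D1 at week 48 and with a compliance-based per-protocol set. For boys removed, the week-48 value would be imputed or, in the sensitivity analysis, carried forward, and this can bring on-drug progression into the estimate.

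The likely size is modest: about 0.2 to 0.9 D1 points on a planned 4.5, if 5% to 20% of the tamoxifen arm stops, loses all benefit and is imputed like completers. It is half of that if they keep half of the effect. These shares are assumptions. The direction under carry-forward depends on which arm loses more boys. This should be corrected, because a missed week-48 assessment cannot be recovered later, but it does not invalidate the primary analysis.

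**What to change.** In the Safety assessments section, and in the full protocol if it reads the same way:
1. Remove noncompliance as a reason for termination from the study, and describe stopping study drug and leaving the study as separate events.
2. State that boys who stop drug or are noncompliant keep the scheduled assessments, at minimum the MFM at week 48, unless consent for follow-up is withdrawn or they cannot attend.
3. In the Primary analysis section, state that these observed week-48 values are used in the primary analysis.

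The reasons for stopping study drug are left as they are. The cost is a short amendment and a few visits off drug that are already in the schedule. The estimated difference may come out somewhat smaller. The sample size need not change. If the full protocol already contains this rule, only the sentence on noncompliance needs to be brought into line with it.
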